# Financially incentivized knowledge assessments to improve provider compliance with treatment guidelines: a cluster-randomized controlled trial

**DOI:** 10.1186/s13063-022-06129-8

**Published:** 2022-03-21

**Keywords:** Quality of care, Health care worker knowledge, IMCI, Financial incentives, Vignettes, Under-5 mortality

## Abstract

**Background:**

Despite increasing access to health care, under-5 mortality remains high in many parts of Sub-Saharan Africa. Interventions to improve quality of care have mostly focused on additional training for medical staff, but generally shown little impact. We will assess the impact of financially incentivized quarterly provider knowledge assessment on compliance with Integrated Management of Childhood Illness (IMCI) protocols in Congo, DRC.

**Methods:**

Out of a total of 1738 facilities currently receiving results-based financing under an ongoing health financing program, 110 facilities were chosen for this study. All health care workers providing outpatient services to children under age 5 in these facilities will be included in the study. Facilities were randomized with equal probability to control and treatment. Treatment facilities will receive quarterly medical staff knowledge assessments using interactive vignettes. Performance on these vignettes will be rewarded through financial bonus payments to facilities. A baseline survey of health worker knowledge was conducted in 2018. An endline assessment is scheduled to start in the second half of 2021. The primary outcome of interest is health worker compliance with Integrated Management of Childhood Illness (IMCI) guidelines. Compliance will be verified through direct observation of medical staff-patient interactions.

**Discussion:**

This is to our knowledge the first trial assessing whether linking health financing to health care worker performance on knowledge assessments can increase compliance with under-5 case management protocols.

**Trial registration:**

ClinicalTrials.gov NCT04634019. Registered on November 18, 2020.

## Administrative information

Note: the numbers in curly brackets in this protocol refer to SPIRIT checklist item numbers. The order of the items has been modified to group similar items (see http://www.equator-network.org/reporting-guidelines/spirit-2013-statement-defining-standard-protocol-items-for-clinical-trials/).

## Introduction

### Background and rationale {6a}

Despite major reductions in child health over the past two decades, under-5 mortality remains high, with an estimated 5.6 million deaths globally in 2016 [1]. Major efforts will be necessary to reach the rather ambitious Sustainable Developmental Goal targets for child survival in West and Central Africa, where the under-5 mortality rate was estimated at 98.7 per 1000 live births in 2015 [2].

A growing body of evidence shows that the majority of under-5 deaths occur after children are seen by health care workers [3–5], suggesting major gaps in the quality of care obtained at health facilities [6–8]. Several initiatives have sought to improve the average quality of care through often costly models of training and supervision but generally found little impact on quality of care [9]. Evidence on alternative models such as quality improvement collaboratives or process monitoring remains somewhat mixed [10, 11].

In this trial, we assess the impact of financially incentivized quarterly knowledge assessments on health care worker compliance with the IMCI guidelines in the context of the Democratic Republic of Congo (DRC).

### Objectives {7}

The main objective of this study is to assess whether making health financing streams conditional on health care worker performance on knowledge assessments can increase health care worker compliance with under-5 case management guidelines.

### Trial design {8}

This trial is designed as an open-label parallel two-group cluster randomized trial with a 1:1 allocation ratio.

## Methods: participants, interventions, and outcomes

### Study setting {9}

This trial will be conducted in DRC and is nested within an ongoing results-based financing program in the provinces of Kwango, Kwilu, and Mai-Ndombe in DRC.

Despite the rapid economic growth in recent years and some improvements in some human development indicators, the DRC has some of the worst health and nutrition indicators in the world. Life expectancy was 58 years only in 2016, and under-five mortality was estimated at 88 deaths per 1000 [12]. The maternal mortality ratio is 670 per 100,000 live births.^1^ Chronic malnutrition among children under five is common with an estimated 42.7% stunted according to the 2014 DHS, and almost half of children under five are moderately or severely anemic [13]. Evidence from a recent facility survey suggests that general health care worker compliance with under-5 treatment protocols is very low [14] and that areas with low compliance on average face higher mortality rates [15].

### Eligibility criteria {10}

All health care workers (medical doctors, nurses, and other clinical staff) providing outpatient care to children under age 5 in 110 randomly selected health facilities will be eligible for the study.

### Who will take informed consent? {26a}

Surveyors (study staff) have training either as nurses or medical doctors and will be specifically trained for these assessments. At the beginning of each sick child clinic visit, surveyors will ask both the child’s caregiver and the attending health worker to consent to them sitting in (and documenting) the medical consultation.

### Additional consent provisions for collection and use of participant data and biological specimens {26b}

No additional consents will be collected.

### Interventions

#### Explanation for the choice of comparators {6b}

In order to make the treatment and control areas as comparable as possible, the study focused only on facilities previously enrolled in a results-based financing program. Under this program, quarterly payments are made to all facilities based on the number or pre-specified services delivered as well as a generic quality score. Facilities in the control group thus are identical in terms of the general monitoring and reporting—the only difference is that a part of the quarterly performance-based payments is made conditional on knowledge test performance in the 55 facilities randomly selected for this intervention.

#### Intervention description {11a}

The intervention is a quarterly payment to the health facilities linked to the performance of a randomly selected health care worker on a knowledge-based assessment performed each quarter.

Health facilities in the intervention group will receive a supervision visit each quarter. During the supervision visits, one health care worker is randomly chosen for the knowledge assessments and is tested on two randomly chosen vignette cases. For the intervention, 12 clinical vignettes were created. These vignettes cover typical patient cases such as malaria, diarrhea, and respiratory infections and assess health workers’ ability to correctly diagnose and treat hypothetical questions. All patient scenarios were generic and covered typical symptoms seen in everyday clinical practice without any particular adaptations to local settings.

All medical staff members were informed that there would be a knowledge assessment based on these vignettes every 3 months and that the results of this assessment would determine the total bonus payment made to the facility.

In order to create a quarterly performance score, the scores on the two vignettes are then averaged. Fifty percent of the overall facility quality score is determined by the general quality checklist that captures the basic structural and process features of the facility. The remaining fifty percent are directly determined by the health care workers’ performance on the knowledge assessments. If the overall quality score is below 50%, no quality payments are made. If the quality score is ≥ 50%, facilities can receive a top-up payment of up to 25% of the quantity-based payments. The total bonus percentage is determined by multiplying the quality score (with ranges between 0 and 100%) with the maximum 25% bonus. As summarized in Fig. 1, any facility with a score below 50% does not get any bonus. A quality score of 50 results in a bonus of 25% × 0.5 = 12.5% − a quality score of 100 results in 25% × 1 = 25% bonus.

**Fig. 1 Fig1:**
[figure not shown]
Incentive structure

The knowledge assessments started in the last quarter of 2018 after the completion of the baseline survey. Figure 2 summarizes the overall timeline of the study as well as key measurement points.

**Fig. 2 Fig2:**
[figure not shown]
SPIRIT overview over study activities

#### Criteria for discontinuing or modifying allocated interventions {11b}

No such criteria were established.

#### Strategies to improve adherence to interventions {11c}

The knowledge assessment intervention is embedded in the larger PBF program supervised by the Ministry of Health with support from the World Bank. Completion of the knowledge assessment tests is required in order to determine the quarterly financial transfers to the selected facilities and strictly enforced. A robust monitoring system has been developed for the program as the data is used to determine financial transfers to health facilities. Moreover, the knowledge assessment tests are conducted with tablets, and the data is uploaded to the project portal.

#### Relevant concomitant care permitted or prohibited during the trial {11d}

All subjects participating in the trial will have access to routine health care services throughout the study.

#### Provisions for post-trial care {16}

None.

#### Outcomes {12}

The primary study outcome is compliance with under-5 diagnostic guidelines. Compliance will be measured through up to 8 direct observations of under-5 sick child visits at each facility collected over a 4-day period. For each visit, 10 diagnostic process steps will be measured. Compliance will be defined as at least 8 out of 10 diagnostic processes completed.

Secondary outcomes will be health care worker’s knowledge of IMCI protocols and compliance with the IMCI treatment guidelines. IMCI knowledge will be assessed through a series of vignettes provided to the medical staff. For compliance with treatment guidelines, we will focus on the administration of antibiotics and anti-malarials and referrals to higher level health centers as well as compliance with all diagnostics steps specified in the IMCI guidelines.

Primary and secondary outcomes will be measured as part of a facility survey that will be conducted between May and December 2021. All facilities in the treatment and control areas will be visited by an assessor team for 3–5 days, who directly observe all under-5 sick child visits up to the targeted 8 observations during this facility visit. For smaller facilities, we expect only about one visit per day—for larger facilities, the target of 8 visits can likely be completed within less than two days.

Similar assessments have been conducted through a baseline survey in 2018. These prior assessments will be used to assess baseline balance; the average 2018 quality scores will also be used as controls in adjusted impact estimates.

#### Participant timeline {17}

Baseline facility assessments in the targeted facilities were conducted in 2018. The knowledge assessment was integrated into the quality scoring of selected facilities since the last quarter of 2018. The data collection to determine the intervention’s impact is currently scheduled to be collected in the third and fourth quarters of 2020.

#### Sample size {14}

A total of 110 facilities participate in the trial. Out of these 110, 50% will be randomly selected for the treatment. Within each facility, up to 8 under-5 sick child visits will be observed. We anticipate an average of 6 direct observations in each facility, resulting in a sample of 660 direct observations for our primary outcome. At baseline, compliance with diagnostic protocols was 10%. The study is powered to detect a 15% point increase in diagnostic compliance (from 10 to 25%) with *p* = 0.9, assuming alpha = 0.05 and an intra-class correlation of 0.2 (DEFF of 2).

#### Recruitment {15}

All targeted facilities had previously been enrolled in the larger RBF program and were randomly selected for this sub-study. To collect data on the quality of under-5 consultations, the study team will spend four full days at each facility observing health care workers during their outpatient consultations with children under the age of 5 years. Based on previous studies in this area, we do not anticipate refusals to be a major challenge.

### Assignment of interventions: allocation

#### Sequence generation {16a}

Randomization was done at the health facility (cluster) level. Within each health zone, 50% of health centers were randomly selected for the intervention using a simple random number draw created in the Stata statistical software package by GS.

#### Concealment mechanism {16b}

Given the personal interactions required for the intervention, all treated health care workers will be fully aware of this program. Assessors conducting the direct observations will however not be informed regarding the treatment status of the facilities surveyed.

#### Implementation {16c}

All facilities had previously been enrolled in the PBF program. Random assignment of the intervention was based on a random number draw created by GS. Selected facilities were then visited by the project team and introduced to the intervention.

### Assignment of interventions: blinding

#### Who will be blinded {17a}

Only the outcome assessors will be blinded to the treatment. All health care workers in the intervention group will be fully aware of the program and treatment allocation.

#### Procedure for unblinding if needed {17b}

NA—health care workers will be fully aware of the treatment, and we do not foresee any reasons for unblinding assessors.

### Data collection and management

#### Plans for assessment and collection of outcomes {18a}

The data collection tools are based on tools developed by the Health Results Innovation Trust Fund for the portfolio of impact evaluations of results-based financing projects (https://www.rbfhealth.org/resource/impact-evaluation-toolkit-provides-hands-guidance). The tools that were further calibrated to local settings are part of the baseline survey conducted in 2015. All tools have been tested through pre-study pilots as well as through the baseline survey and the midline survey in 2015. A copy of the direct observation tool is in the Appendix of this document.

#### Plans to promote participant retention and complete follow-up {18b}

We do not foresee any closure of facilities. It is possible that some of the health care workers who were assessed as part of the knowledge tests no longer work at their prior facilities. This will not affect the sample size overall but will be considered when analyzing the data (larger treatment effects expected for medical staff directly selected for the knowledge test).

#### Data management {18}

All data will be collected electronically using the Open Data Kit (ODK) platform. The ODK software allows to enhance data quality through pre-specified range checks as well as internal consistency checks.

Data will be stored at an encrypted local server. Only the PIs will have access to the identified data, and they will de-identify the data before sharing it with the rest of the research team.

#### Confidentiality {27}

All personal information will be removed from data files prior to analysis.

#### Plans for collection, laboratory evaluation, and storage of biological specimens for genetic or molecular analysis in this trial/future use {33}

NA—no biological specimens will be collected or analyzed as part of this trial.

## Statistical methods

### Statistical methods for primary and secondary outcomes {20a}

Multi-level regression models will be used to analyze the primary and secondary study outcomes. The primary outcome (compliance) will be a binary indicator for (observed) the health care worker completing at least 8 out of 10 diagnostic processes foreseen in the IMCI guidelines during an observed consultation. This indicator will be regressed against the randomized facility-level treatment. The empirical model will look as follows:
$$ {Y}_{if}=\alpha +\beta {V}_f+{\varepsilon}_{if} $$

where *Y*_*if*_ is the quality score (1 if compliant, 0 otherwise) of consultation *i* observed in facility *f*, and *V*_*f*_ is an indicator for facilities having received the vignettes intervention (*V* = 1 if yes and 0 otherwise). *β* is the main parameter of interest and captures the changes in the average quality or compliance in response to the intervention.

The secondary outcomes will be continuous knowledge and compliance scores, which will be based on a detailed assessment of medical staff. The unit of analysis for the knowledge outcome is a health care worker rather than a single consultation, with up to 5 health care workers assessed in each facility.

To account for the treatment assignment at the facility level, standard errors will be clustered at the facility level using Huber’s cluster-robust standard errors in all analyses.

Given that facilities were randomly assigned to treatment and control groups, the risk of residual confounding is low—we will however also estimate a series of adjusted models to ensure the robustness of our results as explained in the next paragraph.

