### Methods for additional analyses (e.g., subgroup analyses) {20b}

To improve the precision of our estimates, we will also estimate the adjusted models where we control for health care worker characteristics (age, training, position, and time at the facility) as well as facility characteristics including facility quality scores at baseline.

In addition, we will conduct a subgroup analysis comparing only medical staff members that were directly assessed in treatment facilities to medical staff in the control group. We will also conduct a stratified analysis at the hospital and health center levels.

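### Allocation was stratified by health zone, but the printed primary model has no zone term; if compliance differs between zones, the reported standard error is conservative

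*Protocol article*

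**What the plan says.** Protocol article, Sequence generation {16a}: "Randomization was done at the health facility (cluster) level", and "Within each health zone, 50% of health centers were randomly selected for the intervention". Health zone is therefore a stratification factor of the design.

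Statistical methods for primary and secondary outcomes {20a}: "Multi-level regression models will be used to analyze the primary and secondary study outcomes". The levels are not named. Of the binary compliance indicator the section says: "This indicator will be regressed against the randomized facility-level treatment". The printed equation for consultation *i* in facility *f* is Y_if = α + βV_f + ε_if, where V_f marks the intervention facilities. On variance, "standard errors will be clustered at the facility level using Huber’s cluster-robust standard errors in all analyses". No zone term or zone subscript appears.

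Methods for additional analyses {20b}: the adjusted models, which are meant to improve precision, control for "health care worker characteristics (age, training, position, and time at the facility") and for "facility characteristics including facility quality scores at baseline". Zone is not named, but the facility list is open-ended.

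**The concern.** When half the facilities in each zone go to each arm, zone-level differences in compliance largely cancel from the comparison of arms. The true sampling variance of β then contains little or no between-zone variation. A standard error from a model without zone still counts that variation, because it sits in the residuals. If zones differ, the confidence interval is wider than it need be and the test runs below its nominal 5%.

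At stake is a needlessly wide interval in the case where it could matter: a true effect smaller than planned and a borderline result. The direction is conservative, so a false-positive claim is not the risk.

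**Working it through.** **Inputs from Sample size {14}.** 110 facilities, taken as 55 per arm; 6 visits per facility on average; 660 observations, 330 per arm; ICC 0.2; alpha 0.05 (two-sided assumed); compliance 10% vs 25%. **Assumed:** the share *s* of between-facility variance that lies between zones, because neither it nor the number of zones is given; equal cluster sizes; an exact 50:50 split within each zone; a normal approximation.

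**The plan's own figures.** DEFF = 1 + (6 − 1) × 0.2 = 2.0, as stated. The effective sample is 330/2 = 165 per arm, which gives power 0.951 (pooled variance) or 0.955 (unpooled). The stated 0.9 is therefore a floor with about 5 points to spare.

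**Width of the standard error.** With total variance 1, a facility mean has variance 0.2 + 0.8/6 = 0.333. Within zones it is 0.2(1 − s) + 0.8/6. On the DEFF scale, the model without zone reports 2.0, while the true value under zone-balanced allocation is 2.0 − 6 × 0.2 × s. The SE ratio is √(2.0/true DEFF), and the type I error is 2[1 − Φ(1.96 × ratio)].

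| s | true DEFF | SE ratio | type I error |
|---|---|---|---|
| 0 | 2.00 | 1.00 | 5.0% |
| 0.10 | 1.88 | 1.03 | 4.3% |
| 0.25 | 1.70 | 1.08 | 3.4% |
| 0.50 | 1.40 | 1.20 | 1.9% |

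**Power.** Let v = [p1(1 − p1) + p2(1 − p2)]/330 and d = p2 − p1. Without zone, power is Φ{(d − 1.96√(2v))/√(v × true DEFF)}. With zone, it is Φ{d/√(v × true DEFF) − 1.96}. For 10% vs 25%, v = (0.09 + 0.1875)/330. At s = 0.50 the reported SE is 0.0410 and the true SE 0.0343. Power without zone is Φ{(0.15 − 1.96 × 0.0410)/0.0343} = 0.979; with zone it is Φ{0.15/0.0343 − 1.96} = 0.992.

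| s | 10% vs 25%: without / with zone | 10% vs 20%: without / with zone |
|---|---|---|
| 0 | 0.955 / 0.955 | 0.73 / 0.73 |
| 0.10 | 0.960 / 0.965 | 0.74 / 0.76 |
| 0.25 | 0.967 / 0.978 | 0.75 / 0.80 |
| 0.50 | 0.979 / 0.992 | 0.77 / 0.87 |

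A simulation of 110 facilities in 10 or 25 assumed zones agrees. With s = 0.50, null rejection without zone was 2.7% and 2.1%. At the planned effect, power rose from about 0.975 to 0.99 when zone was added. With s = 0, the two models performed alike.

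**Does the obvious remedy hold its size?** The usual cluster-robust factor is G/(G − 1) × (N − 1)/(N − p), for G facilities, N = 6G visits and p parameters (the zones plus treatment). It counts zone parameters against visits, although each one is paid for in facilities. The factor needed is close to G/(G − p). The last column is 2[1 − Φ(1.96 × √(usual/needed))].

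| assumed layout | usual factor | G/(G − p) | approximate type I error, usual factor |
|---|---|---|---|
| 55 zones of 2 (G = 110, p = 56) | 1.10 | 2.04 | 15% |
| 27 zones of 4 (G = 108, p = 28) | 1.05 | 1.35 | 8% |
| 11 zones of 10 (G = 110, p = 12) | 1.03 | 1.12 | 6% |

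Simulation under the null gives the same pattern: about 15%, 8% and 5 to 6.5%. Using G/(G − p) with t on G − p degrees of freedom brings all three layouts back to about 5%.

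**The case against.** The strongest reply is that nothing here can mislead in the dangerous direction. Allocation is 1:1 within zones, no bias in β is shown, and type I error is at or below 5%. If zones do not differ, the loss is zero. At the planned effect, power without zone is at least 0.95 for every share considered, above the stated 0.9. All of this stands, and it limits the severity.

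A reader might infer that the precision gained by stratifying is thrown away. It is not. Stratified allocation still reduces the true variance of β, and power without zone rises with the zone share (0.955 to 0.979). Only the reported standard error fails to credit the gain.

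A reader might also infer that the adjusted models exclude zone. The covariate list is open, so zone is unnamed rather than ruled out, and baseline quality scores may absorb part of any zone difference. The unnamed levels of the multi-level models leave similar room. Exact covariates are often left to an analysis plan, which is not shown here. That excuses the adjusted models. It does not settle the primary model, whose equation is printed in full without zone.

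The last objection is that zone indicators can do harm: with many small zones and the usual correction, a conservative test becomes an anti-conservative one. This is correct, and it changes the remedy.

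**Conclusion.** The point holds as a mismatch between design and analysis: allocation was stratified by health zone, and the stated primary model ignores it. The consequence depends on how far compliance varies between zones, which the document does not say. For zone shares from 0 to 50%, the standard error is too wide by a factor of 1.00 to 1.20 and true type I error runs from 5.0% down to 1.9%. Power lost is 0 to about 1.3 points at the planned effect. It becomes material mainly for smaller effects: at 10% vs 20%, about 5 points at a 25% share and 10 points at 50%.

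The documents do not support a claim that power is certainly wasted, that β is biased or that the trial is underpowered. This should be fixed; it is not essential to the trial's validity.

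**What to change.** Add health-zone indicators to the primary model, Y_if = α + βV_f + γ_zone(f) + ε_if, and to the secondary and adjusted models. Keep clustering at facility level. Specify a small-sample correction that counts the zone parameters at cluster level: for example G/(G − p) with t on G − p degrees of freedom, or a bias-reduced cluster-robust variance. State the number of zones and how any zone with only one arm is handled, since such a zone carries no information on β once zone is in the model. If zone is to be left out, give the reason.

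The cost is one model term and a sentence or two on variance estimation, plus one degree of freedom per zone. That is small with few large zones but not negligible with many small ones (p = 12 against p = 56 of 110 facilities in the layouts above). The choice should be fixed before the arms are compared.

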### Methods in analysis to handle protocol non-adherence and any statistical methods to handle missing data {20c}

We do not anticipate major missingness on our main outcomes. For the covariates in the adjusted models, we will use multiple imputations by chained equations.

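### The treatment regressor is defined by receipt in one sentence and by randomisation in another, and the multi-level label does not match the printed single-level model; a modest inconsistency to reconcile

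*Protocol article*

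**What the plan says.** Everything that defines the primary analysis is in the protocol article, section {20a}.

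- **Model label:** "Multi-level regression models will be used to analyze the primary and secondary study outcomes".
- **Equation**, introduced by "The empirical model will look as follows": Y_if = α + βV_f + ε_if. It has a binary outcome, an identity link, one error term and no facility-level term.
- **Variance:** "standard errors will be clustered at the facility level using Huber’s cluster-robust standard errors in all analyses".
- **Treatment, in the sentence leading to the equation:** "This indicator will be regressed against the randomized facility-level treatment".
- **Treatment, in the definition of the symbol:** V_f "is an indicator for facilities having received the vignettes intervention".

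Three other sections bear on whether the two treatment definitions could diverge. Section {11c} says of the assessments: "Completion of the knowledge assessment tests is required in order to determine the quarterly financial transfers to the selected facilities and strictly enforced". Section {18b} adds: "We do not foresee any closure of facilities". Section {20c} has non-adherence in its title, but its text deals only with missing data, beginning "We do not anticipate major missingness on our main outcomes". Section {16a} states that half of the health centers in each health zone were drawn for the intervention.

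**The concern.** A programmer codes a variable from its definition, and the definition given for V_f is receipt. An assigned facility in which the assessments were never run would then be coded 0 and analysed with the controls. Facilities that fail to run a supervised quarterly programme may well differ from the rest in quality of care, so moving them across arms gives up the protection of randomisation. Receipt is also not defined for an intervention delivered every quarter since late 2018: one assessment, most of them, or all of them could each count. Coding by assignment needs no such rule.

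The second mismatch concerns the model. A multi-level model normally carries a facility-level random effect, and the printed equation has none. Two analysts could fit different models and each cite section {20a}.

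**Working it through.** **Plan's own figures.** Section {14} gives 10% against 25%, a difference of 15 points, with 110 facilities, an average of 6 observations each (660 in all, 330 per arm) and an ICC of 0.2. The design effect is 1 + (6 − 1) × 0.2 = 2.0, as stated. The effective size is 330/2 = 165 per arm, which gives two-sided power of 0.951. The stated 0.9 is therefore not reproduced, but the difference is in the safe direction and nothing below depends on it.

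**Received against randomised.** Let k of the 55 assigned facilities not receive the intervention and comply at q%. The other assigned facilities comply at 25% and the 55 controls at 10%, with equal facility sizes. The values of k and q are assumptions; the documents give none.

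- As randomised: [(55 − k) × 25 + k × q]/55 − 10
- As received: 25 − [55 × 10 + k × q]/(55 + k)

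| k | q | As randomised | As received | Gap |
|---|---|---|---|---|
| 0 | – | 15.0 | 15.0 | 0 |
| 5 | 10% | (1250 + 50)/55 − 10 = 13.6 | 25 − 600/60 = 15.0 | 1.4 |
| 5 | 5% | (1250 + 25)/55 − 10 = 13.2 | 25 − 575/60 = 15.4 | 2.2 |

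With q = 10%, the as-received contrast stays at 15.0 and the as-randomised contrast is 15 × (1 − k/55). That gives 14.7, 14.2, 13.6 and 12.8 points for k = 1, 3, 5 and 8, so gaps of 0.3 to 2.2 points. Under the same assumptions, power for the as-randomised contrast is 0.915 at k = 5 and 0.885 at k = 8. Coding by assignment costs little.

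**Multi-level against cluster-robust, identity link.** 150 trials were simulated, each with 110 facilities of 4 or 8 visits, ICC 0.2, and 10% against 25% compliance.

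| | Linear mixed model | OLS with clustered errors |
|---|---|---|
| Mean β | 0.149 | 0.148 |
| Mean SE | 0.0413 | 0.0416 |

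The two estimates correlated at 0.98. They separate if the effect varies with facility volume, because OLS weights a facility by m and the mixed model by m/[1 + (m − 1) × 0.2], which is 2.5 for m = 4 and 3.33 for m = 8. Assume effects of 20 points in 4-visit and 10 points in 8-visit facilities, in equal numbers:

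- OLS: (4 × 20 + 8 × 10)/12 = 13.3
- Mixed model: (2.5 × 20 + 3.33 × 10)/5.83 = 14.3

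**The case against.** The strongest reply is that the rest of section {20a} leaves little doubt about what is meant. The preceding sentence says randomised. Clustering is justified by assignment at facility level, and the low risk of confounding is attributed to random assignment, which makes sense only if V_f is assignment. Section {6b} identifies the intervention group with the 55 randomly selected facilities. No as-treated analysis of facilities is described anywhere. Sections {11c} and {18b} expect full delivery and no closures, and then the gap is zero. All of this stands and limits the severity. It does not remove the conflict, because those sections state expectations and the formal definition still says received. The silence of section {20c} on non-adherence is not counted as a defect, since such a rule is commonly left to an analysis plan. It means only that nothing there settles the coding.

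A reader might go further and infer that the two descriptions of the model imply different estimands, for example a random-intercept logistic odds ratio in place of a risk difference. For 10% against 25% the marginal odds ratio is (0.25/0.75)/(0.10/0.90) = 3.0. The facility-conditional one would be about 3.4 with ICC 0.2 on the latent scale, or 4.2 with ICC 0.2 on the probability scale. The document does not support that inference. It mentions neither a logit link nor an odds ratio, β is described as a change in average compliance, and section {14} powers the trial on percentage points. All of these point to a marginal risk difference.

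**Conclusion.** Both inconsistencies are real, and both lie in the one section that defines the primary analysis. Their consequences are conditional. The coding of V_f matters only if some assigned facilities do not receive the intervention, which the protocol does not expect. For 5 of 55 the gap would be about 1.4 to 2.2 points on an effect of 15, under the assumed compliance rates. The multi-level label makes almost no difference under the printed identity link unless effects vary with facility volume, where the assumed example gives about 1 point. The scale of the result would change only under a logistic reading that the text does not state. It would be too strong to say that the plan specifies two different estimands or that its headline result is at serious risk. Severity is minor to moderate: worth correcting because the as-received definition is wrong on its face and the correction is nearly free.

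**What to change.** In section {20a}:

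1. Define V_f = 1 if facility f was randomised to the vignette intervention and 0 otherwise, regardless of whether or how often the assessments were delivered.
2. Name one primary model: the printed linear model for the risk difference, with facility-clustered standard errors. Delete multi-level, or explain what it refers to.
3. Add health-zone effects to that model, because section {16a} randomised within health zones. This aligns the analysis with the design and is separate from the two wording conflicts.

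The cost is a few sentences and no new data beyond each facility's zone and allocation, which the randomisation already holds. Section {12} places endline collection in May to December 2021 and the protocol version is dated 22 February 2022, so the change should be recorded as made without reference to results by arm.
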